## Abstract

**Background:**

Recent evidence supports hippocampal avoidance with whole brain radiotherapy (HA-WBRT) as the recommended treatment option in patients with good prognosis and multiple brain metastases as this results in better neurocognitive preservation compared to whole brain radiotherapy. However, there is often poor tumour control with this technique due to the low doses given. Stereotactic Radiosurgery (SRS), a form of focused radiotherapy which is given to patients who have a limited number of brain metastases, delivers a higher radiation dose to the metastases resulting in better target lesion control. With improvements in radiation technology, advanced dose-painting techniques now allow a simultaneous integrated boost (SIB) dose to lesions whilst minimising doses to the hippocampus to potentially improve brain tumour control and preserve cognitive outcomes. This technique is abbreviated to HA-SIB-WBRT or HA-WBRT+SIB.

**Methods:**

We hypothesise that the SIB in HA-SIB-WBRT (experimental arm) will result in better tumour control compared to HA-WBRT (control arm). This may also lead to better intracranial disease control as well as functional and survival outcomes. We aim to conduct a prospective randomised phase II trial in patients who have good performance status, multiple brain metastases (4–25 lesions) and a reasonable life expectancy (> 6 months). These patients will be stratified according to the number of brain metastases and randomised between the 2 arms. We aim for a recruitment of 100 patients from a single centre over a period of 2 years. Our primary endpoint is target lesion control. These patients will be followed up over the following year and data on imaging, toxicity, quality of life, activities of daily living and cognitive measurements will be collected at set time points. The results will then be compared across the 2 arms and analysed.

**Discussion:**

Patients with brain metastases are living longer. Maintaining functional independence and intracranial disease control is thus increasingly important. Improving radiotherapy treatment techniques could provide better control and survival outcomes whilst maintaining quality of life, cognition and functional capacity. This trial will assess the benefits and possible toxicities of giving a SIB to HA-WBRT.

**Trial registration:**

Clinicaltrials.gov identifier: NCT04452084. Date of registration 30th June 2020.

## Introduction

### Background

The management of brain metastases presents a significant challenge in oncology. Whole brain radiation therapy (WBRT) is widely given to improve neurological symptoms, stop brain metastasis progression and possibly prolong survival. Unfortunately, neurocognitive functional decline is reported in a significant number of patients who undergo WBRT at rates of 31–57% at 3 months and 48–89% at 1 year [1].

The hippocampus plays a key role in learning, memory and cognitive function [2–4]. The significance of hippocampi radiation in clinical studies is emerging. Gondi et al. showed that a dose of > 7.3Gy to at least 40% of the hippocampus resulted in a significant decline in delayed recall in adult brain cancer patients [5].

A recent phase 3 trial, NRG-CC001, randomised 518 patients to Hippocampal avoidance-WBRT (HA-WBRT) against standard WBRT. Cognitive endpoints were measured using a test battery of Hopkins Verbal Learning Test-Revised (HVLT-R), Controlled Oral Word Association, and Trail Making Test (TMT) Part A & B. At a median follow-up for alive patients of 7.9 months, a significant reduction in cognitive failure risk was noted (HR, 0.76; *P* = 0.03) in the HA-WBRT arm. This difference was most significant in the 4-month TMT Part B scores and the 6-month HVLT-R score. The median overall survival (OS) and progression free survival (PFS) did not differ and there was no increase in hippocampal relapses. However notably, OS and PFS in the HA-WBRT arm were poor at 6.3 months and 5.0 months respectively [6].

This trial introduced HA-WBRT as a new standard option in patients with multiple brain metastases and good prognosis. However, some clinicians would still favour the use of Stereotactic Radiosurgery (SRS) over HA-WBRT in patients with low volume brain metastases. The reasons could possibly be better cognitive sparing or tumoral control due to the higher ablative doses used in SRS. Several trials are underway comparing the use of HA-WBRT against SRS (ClinicalTrials.gov identifier: NCT03550391, NCT03075072 and NCT04277403).

### Rationale

In the landmark RTOG 95–08 trial which compared an SRS boost vs. no boost in patients undergoing WBRT, the patients in the boost arm had improved local control rates, better functional autonomy and reduced steroid need with few toxicities [7]. OS was also improved in some patients [8, 9]. With current dose-painting radiotherapy planning techniques, we are now able to deliver a simultaneous integrated boost (SIB) dose to the lesions while giving HA-WBRT, a technique abbreviated as HA-SIB-WBRT or HA-WBRT+SIB.

Several single-arm prospective studies looked at the use of WBRT+SIB or HA-SIB-WBRT in variable patient cohorts with SIB doses of 40–52.5Gy in 10–15 fractions [10–15]. The reported intracranial PFS was noted to be as high as 13.5 months with few ≥Grade 3 toxicities (≤6.5%), making it a potentially viable option. In a propensity score-matched comparison against WBRT, Popp et al. reported significantly improved local tumour control rates, intracranial PFS, reduction in neurological deaths and even better OS [12]. This has led the group to continue to a phase II HIPPORAD Trial comparing HA-WBRT+SIB against WBRT+SIB (German Clinical Trials Registry: DRKS00004598) [16].

Given that brain metastases are being detected earlier and better systemic options have extended the survival in many patients, the need to maintain functional independence and brain disease control is increasingly important. In the management of brain metastases, there is still an unmet need for patients with good prognoses but are unable to receive SRS to have better intracranial disease control over the new standard of HA-WBRT. It is thus important to assess if the addition of a SIB will improve the outcomes of HA-WBRT.

To our knowledge, there is no prospective trial underway comparing HA-SIB-WBRT against HA-WBRT. We thus aim to test if there is a clinical benefit for the additional SIB in HA-WBRT. In preparation for this trial, we performed a planning study to test the feasibility of dosimetric targets set for HA-SIB-WBRT in 5 patients with different tumour numbers, volumes and locations as well as experimented with various treatment planning techniques [17]. From this, we were then confident in our ability to proceed with our study.

We hypothesise that HA-SIB-WBRT will be able to increase both target tumour and intracranial disease control compared with HA-WBRT alone. This, therefore, has the potential to impact on survival outcomes whilst maintaining cognitive function and quality of life.

### Objectives

The purpose of the study is to assess the impact that adding SIB to standard of care treatment (HA-WBRT) has on local control, survival outcomes, cognition and other patient reported outcome measures (PROMs).

### Study design

This study will be conducted as a single centre prospective randomised phase II trial in patients with multiple brain metastases and good prognosis (> 6 months). The patients will be compared between the 2 arms: HA-WBRT (control) vs. HA-SIB-WBRT (experimental). The target recruitment is 100 patients over 2 years.

## Methods: participants, interventions and outcomes

### Study setting

The trial will be conducted at the National Cancer Centre Singapore, which is the largest cancer centre in the country. The study workflow is depicted in Fig. 1.

**Fig. 1 Fig1:**
[figure not shown]
Project Schema

### Eligibility criteria

Participants will be recruited if they meet the criteria set out in Table 1 below.

**Table 1 Tab1:** Eligibility Criteria

Inclusion Criteria	Exclusion Criteria
• 21–80 years old patients • Radiological confirmed brain metastases (4–25 lesions) • Histologically proven malignancy • ECOG performance status ≤2 • Maximum lesion or cavity size ≤5 cm o For patients with large (≥3 cm) lesions, a neurosurgical consult is recommended due to the increased risk of cerebral oedema o If brain surgery or other invasive procedures are performed, the treatment should begin at least 2-weeks post-procedure • Life expectancy of at least 6 months • Negative serum pregnancy test within 14 days prior to registration for women of childbearing potential • Women of childbearing potential and male participants who are sexually active must agree to use a medically effective means of birth control throughout protocol treatment • Not suitable for or does not want SRS • Agrees to be randomised to either HA-WBRT or HA-SIB-WBRT	• Prior whole brain radiotherapy. o Prior SRS is not an exclusion. Details of treatment must be recorded. • Diffuse leptomeningeal disease • Extensive extracranial disease, not controlled by systemic treatment • Major medical or psychiatric illness, which in the investigator’s opinion would interfere with the completion of therapy and follow up • Dementia, ongoing psychotic episodes or moderate-severe depression (PHQ-9). • Recent stroke in the past 3 months • Symptomatic brain metastases limiting ADLs • Rapid progression of brain lesion • Patients unable to give informed consent • Total tumour planning target volume (PTV) > 60 cc • Radiological evidence of hydrocephalus • Contraindication to Gadolinium contrast-enhanced MRI brain • Patients with diagnoses of small cell carcinoma, lymphoma or primary brain tumour

### Interventions

The control arm in this study is HA-WBRT. This will be given 30Gy in 10 fractions.

The experimental procedure is HA-SIB-WBRT. 40-45Gy in 10 fractions will be used for the SIB boost depending on the location of the lesion. 45Gy was selected as it has a similar biological effective dose (BED 65.2Gy; α/β = 10) to the 21Gy SRS dose. 40Gy (EQD2 60Gy; α/β = 2) was selected for tumours within/ close to organs at risk (OARs) to meet the recommended dose limits of common OARs. Any post-operative cavity will be contoured using consensus guidelines [18]. The cavity will be given a boost of 40Gy due to the high risk of microscopic residual disease and tumour seeding. Any gross residual tumour should be boosted to 45Gy. Further radiotherapy dose guidance is described in Table 2.

**Table 2 Tab2:** Radiotherapy Planning targets, Organs at Risk and Dose Guidance

Volume	Description	Dose Target/ Limits	Variation Acceptable	Notes
GTV_45Gy^b^	Contoured using fused contrast enhanced MRI images.	45Gy 98% covered by 100% dose Hotspot > 110% within GTV	95% covered by 95% dose	Lesion visible on at least 2 scan slices. Coverage to be comprised to meet OAR constraints
PTV_45Gy^b^	GTV + 0-2 mm isotropic margins	45Gy 98% covered by 95% dose	90% covered by 90% dose	Coverage to be comprised to meet OAR constraints
GTV_40Gy^b^	Tumour volume within/ ≤5 mm from OAR	40Gy 95% covered by 95% dose Hotspot > 110% within GTV	90% covered by 95% dose	Lesion visible on at least 2 scan slices. Coverage to be comprised to meet OAR constraints
PTV_40Gy^b^	PTV_40Gy = GTV_40Gy; i.e. no expansion	40Gy 95% covered by 95% dose	90% covered by 90% dose	Coverage to be comprised to meet OAR constraints
GTVall_5mm^b^	All GTVs + 5 mm isotropic margins	–	–	For plan optimisation
Left & Right Hippocampus	Contoured using fused MRI as per RTOG contouring atlas (http://www.rtog.org//corelab/contouringatlases/hippocampalsparing.aspx), excluding any GTV	D100% (Dose to 100% volume) ≤ 9Gy Dmax ≤16Gy Dmax ≤33Gy^a^	D100% ≤ 10Gy Dmax ≤17Gy Dmax ≤44Gy^ab^	Dmax to 0.03 cc
Hippocampal Avoidance Zone (HAZ)	Hippocampus + 5 mm isotropic margins	–	–	For plan optimization
Left & Right Optic chiasm	–	Dmax ≤33Gy	Dmax ≤37.5Gy^b^ Dmax ≤40Gy^ab^	Dmax to 0.03 cc
Left & Right Optic nerve	–	Dmax ≤33Gy	Dmax ≤35Gy^b^	Dmax to 0.03 cc
Left & Right Orbits	–	Dmax ≤33Gy	Dmax ≤35Gy^b^	Dmax to 0.03 cc
Left & Right Lens	–	Dmax ≤6Gy	Dmax ≤10Gy^b^	Dmax to 0.03 cc
Brain Stem	–	Dmax ≤33Gy	Dmax ≤37.5Gy^b^ Dmax ≤40Gy^ab^	Dmax to 0.03 cc
Left & Right Cochlear	–	Dmax ≤33Gy	Dmax ≤35Gy^a^	Dmax to 0.03 cc
Brain	Brain parenchyma down to cranial margin of dens	30Gy	–	–
PTV_Brain	(Brain + 3 mm isotropic margins) – (GTVall_5mm^b^ + HAZ)	95% of volume covered by 30Gy D2% ≤ 37.5Gy D98% (Dose to 98% of volume) ≥ 25Gy	90% of volume covered by 30Gy D98% ≥ 22.5Gy^b^ D2% ≤ 40Gy^b^	–

^a^*Applicable if tumours within/ ≤5 mm from OARs*^b^*Only applicable to HA-SIB-WBRT plans*

Patients whose plans are unable to meet the recommended constraints will not be eligible for the trial and will be dropped out and undergo WBRT or HA-WBRT as standard of care treatment. Patients can also voluntarily or involuntarily drop-out of the trial at any time after enrolment. These patients will not be replaced. The reason for drop-out must be recorded.

All treatment plans in the experimental arm will be reviewed and approved at the weekly Neuro-radiation oncology team audits prior to the start of treatment. Immobilisation will be performed in all patients. Daily image verification by image-guided radiotherapy is required.

All concomitant treatments should be documented. The use of concurrent cytotoxic systemic treatments is not allowed as this could cause additional or unexpected neuro-toxicities. If the participant is on systemic treatments, a treatment break of at least 7 days for immunotherapy or chemotherapy and 3 days for targeted therapy is recommended before and after radiotherapy. Interruptions should be discussed with the patient’s prescribing medical oncologist.

The use of dexamethasone during radiotherapy is not mandatory but is recommended for use if the patient with symptomatic brain metastases, significant cerebral oedema, large tumours or posterior cranial fossa lesions. The concurrent use of memantine for cognitive protection is recommended but not mandated.

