### Assignment of interventions

Patients recruited will be stratified by the number of brain metastases < 10 vs. ≥10. Within each stratum, patients will be randomized in a 1:1 ratio to control vs. experimental arms. Simple randomization will be performed using a computer-generated random sequence allocation. This will be performed by the research coordinator after informed consent has been taken. The allocation sequence is concealed from the investigators. Patients and treating radiation oncologist will not be blinded to the intervention as it was opined that our patients would want to be aware of the treatment received and that unblinding would not significantly affect our primary objective measure.

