## Statistical methods

### Statistical analysis plans

Efficacy analyses will be performed using the intention-to-treat principle. Per-protocol analyses may be performed as secondary analyses. Safety analyses will include all patients who started treatment and will be performed according to the actual treatment received.

The primary endpoint, time to target lesion progression, will be defined as the time from randomisation to target lesion progression. Patients who pass away before documented target lesion progression will be censored at the last brain imaging assessment. Time to target lesion progression will be compared between the 2 treatment groups using a 2-sided log-rank test.

Time to intracranial progression, time to symptomatic brain progression, progression-free survival and overall survival will be defined as the time from randomisation to intracranial progression, symptomatic brain progression, overall progression and death from any cause respectively. All time-to-event endpoints will be summarized using the Kaplan-Meier method. Treatment arms will be compared using log-rank tests and Cox proportional hazards models, adjusting for the stratification variable (number of brain metastases). Other prognostic variables such as histology, ECOG status and disease-specific GPA class may also be included in the Cox models.

Adverse events will be recorded according to CTCAE version 5.0 and summarised by treatment arm.

Cognitive test (HVLT-R and CTT) scores will be standardised based on published norms: (Patient value – Published-norm mean value) ÷ Published-norm standard deviation value. Cognitive deterioration will be defined as a decline of at least 1 SD in score from baseline. FACT-BR scores will be transformed to a 0- to 100- point scale. A 10-point decrease will be considered clinically significant. Deterioration in functional independence will be defined as a decline of at least 10% in the Barthel ADL index from baseline.

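### Dropping patients whose plans miss the dose constraints reads as an arm-dependent exclusion after randomisation, at odds with the intention-to-treat statement

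*Protocol article*

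**What the plan says.** All references are to the protocol article.

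- **Interventions, text below Table 2.** "Patients whose plans are unable to meet the recommended constraints will not be eligible for the trial and will be dropped out", after which they "undergo WBRT or HA-WBRT as standard of care treatment". The next sentence adds that patients can also drop out at any time once enrolled. Then: "These patients will not be replaced". The reason for drop-out has to be recorded.
- **Interventions, Table 2.** Footnote b reads "Only applicable to HA-SIB-WBRT plans". It marks every boost GTV and PTV coverage target. It also marks several acceptable variations for organs at risk and for PTV_Brain.
- **Interventions, plan review.** "All treatment plans in the experimental arm will be reviewed and approved" at a weekly team audit. No such review is stated for control plans.
- **Assignment of interventions.** On randomisation: "This will be performed by the research coordinator after informed consent has been taken". Acceptance of a plan is not named as a precondition.
- **Statistical analysis plans.** "Efficacy analyses will be performed using the intention-to-treat principle". Time to target lesion progression, the primary endpoint, runs from randomisation.
- **Sample size.** 60 evaluable patients, raised to 100 for a 40% non-evaluable rate.

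**The concern.** If the plan is made for the assigned technique, its failure is an event after allocation. Calling the patient ineligible at that point lets eligibility depend partly on the arm. Only a SIB plan has boost targets to meet, and a patient whose SIB plan fails may be given HA-WBRT, which is the control treatment. A similar patient allocated to control would simply have stayed in the trial.

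Two things are at stake. First, plans that cannot deliver the boost may belong to patients whose lesions are harder to control. Losing them from one arm would flatter that arm on the primary endpoint. Second, a patient who has left the trial may have no further trial imaging, and an analysis plan cannot restore scans that were never collected. Patients and treating oncologists are not blinded, and dropped patients are not replaced.

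**Working it through.** **1. The plan's own figure reproduces.**
- SIB control at 6 months: 0.50^0.27 = 0.829, matching the stated 83%.
- Events (Schoenfeld): 4 × (1.960 + 0.842)² / (ln 0.27)² = 31.4 / 1.714 = 18.3, so 19.
- Mean 6-month event probability: (0.50 + 0.171) / 2 = 0.335. Then 19 / 0.335 = 56.7, or 58 in equal arms, against the stated 60.
- Total: 60 / (1 − 0.40) = 100.

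The arithmetic is sound. The question is who remains in the comparison.

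**2. Order of events.** Consent comes first, then randomisation. The Interventions section refers to plans by arm and places plan failure beside drop-out following enrolment. Together these point to planning after allocation. The text does not say so outright, and Fig. 1 and Table 3 are not shown.

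**3. Bias if failures are removed from the SIB arm only and SIB has no effect.** The documents give neither the share of unplannable patients (f) nor their relative hazard of target progression (k). Both are assumed.

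Inputs: 50 per arm; monthly hazard ln 2 / 6 = 0.1155 for plannable patients (50% control at 6 months, Sample size section) and k times that for the rest; two-sided 5% log-rank test. For k above 1 the overall control rate is therefore somewhat below 50%.

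The initial hazard ratio is 1 / (1 + f(k − 1)). It moves towards 1 as the harder patients progress. The table shows this ratio and the simulated result with 6 months' follow-up and no deaths.

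| f | k | Initial ratio | Simulated ratio | False SIB win |
|---|---|---|---|---|
| 5% | 1.5 | 1/1.025 = 0.98 | 0.98 | 3.0% |
| 5% | 2 | 1/1.05 = 0.95 | 0.97 | 3.4% |
| 10% | 1.5 | 1/1.05 = 0.95 | 0.96 | 3.6% |
| 10% | 2 | 1/1.10 = 0.91 | 0.93 | 4.6% |
| 20% | 2 | 1/1.20 = 0.83 | 0.86 | 7.1% |
| 20% | 3 | 1/1.40 = 0.71 | 0.79 | 11.4% |
| 30% | 2 | 1/1.30 = 0.77 | 0.79 | 9.9% |
| 30% | 3 | 1/1.60 = 0.63 | 0.70 | 18.2% |

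The nominal false-win chance is 2.5%. Adding deaths (median survival 6.3 months, which the Background gives for the HA-WBRT arm of the earlier phase 3 trial) and following patients for 12 months gives similar results:
- f 5–10%, k 1.5–2: ratio about 0.94–0.98, false win 3–4%.
- f 20–30%, k 2–3: ratio about 0.71–0.87, false win 6–16%.
- Only half of the hard-to-plan patients dropped, f 20–30%, k 2–3: ratio about 0.87–0.94, false win 4–6%.

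With k = 1 the formula gives 1 / (1 + 0) = 1, so removal costs patients but adds little bias. If every patient is kept as randomised, the two-sided type I error stays at about 5%.

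**4. Cost of keeping them.** Let x be the share of the SIB arm that receives HA-WBRT, with no link to prognosis. Then S6 = (1 − x) × 0.829 + x × 0.50, and HR = ln(S6) / ln(0.50).
- x = 10%: S6 = 0.796, HR = 0.33.
- x = 20%: S6 = 0.763, HR = 0.39.

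Simulated power at 6 months:

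| Setting | x = 0 | x = 10% | x = 20% |
|---|---|---|---|
| 30 per arm, no deaths | 80% | 69% | 56% |
| 50 per arm, no deaths | 95% | 90% | 79% |
| 50 per arm, median survival 6.3 months | 88% | about 79% | about 67% |

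**The case against.** The strongest reply is that the text proves less than it suggests. Four parts of it deserve weight.

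- **Arm differences run both ways.** Footnote b also gives SIB plans looser acceptable limits for several organs at risk and for PTV_Brain. Boost coverage may give way to organ limits, and lesions close to such organs have their own target with lower coverage requirements. Control plans can fail the shared limits too. A reader might infer that failures must fall mainly on the SIB arm; that is plausible but not shown. This part stands.
- **Volume limit.** A reader might infer that the exclusion "Total tumour planning target volume (PTV) > 60 cc" acts only in the SIB arm, because Table 2 defines tumour PTVs for SIB plans. The documents do not support that. Table 1 lists it as an entry criterion for every participant, so it removes very large volumes from both arms. It also implies some contouring before entry.
- **Timing.** Ineligibility is screening language. If plans had to be feasible under both techniques before randomisation, the problem would vanish. Nothing in the text says this, so the reply shows ambiguity and does not remove it.
- **Analysis set.** A reader might infer that intention-to-treat is already broken. No sentence removes dropped patients from the efficacy set, and recording reasons without replacing patients is compatible with counting them as randomised. Equally, no sentence says that they are followed. That gap concerns trial conduct, so an analysis plan that is not shown could not fully close it.

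The five-patient planning study cited in the Rationale supports feasibility but gives no failure rate.

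**Conclusion.** The point holds as an unresolved conflict between three sections. Applied as written, the plan-failure rule can remove randomised patients on a criterion that differs by arm, while the efficacy analysis is promised by intention to treat. That plans follow randomisation is the best reading of the text, not a stated fact.

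Neither the direction nor the size of any bias is established. Favouring SIB is the plausible direction, and it needs both more failures in that arm and a worse prognosis among them. With few failures and a modest excess hazard the effect is small. It becomes material only in the 20–30% range with two to three times the hazard, and no figure in the documents places the trial there. The lost imaging is a separate cost that arises whatever the direction.

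No view is taken on the dose constraints themselves.

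**What to change.** Reconcile the Interventions, Assignment of interventions and Statistical analysis plans sections in one of two ways.

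1. **Keep everyone (wording only).** State that every randomised patient stays in the efficacy set in the assigned arm and continues scheduled imaging and visits, whatever plan is delivered. Record a failed plan as a treatment deviation instead of ineligibility, and report the number and reasons by arm.
2. **Decide earlier, where workload allows.** Confirm plan feasibility for every consented patient before randomisation, so that failures leave both arms equally. This moves work forward and adds contouring and SIB planning for patients later allocated to control.

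The trial was recruiting when the article was written, so the second option can cover only patients not yet randomised. Anyone already dropped after allocation should be counted in the assigned arm, using whatever routine scans exist.

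The price of the first option is some dilution of the intention-to-treat effect. State the power expected if 10% or 20% of the SIB arm does not receive the boost beside the 80% in the Sample size section. Neither option requires a change to any dose constraint.
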